## Abstract

Supplemental Digital Content is available in the text

## Introduction

1

### The obesity problem

1.1

Obesity is growing epidemic in developed countries characterized by elevated body mass index (BMI) and associated with numerous health problems including cardiovascular issues (e.g., stroke, coronary disease, hypertension, type 2 diabetes mellitus).^[1,2]^ Obesity exacerbates primary cardiovascular risk factors (lipids, blood pressure, glucose, and inflammation)^[3]^ and contributes 20% of all mortalities^[4]^ and 40% of mortalities due to cardiovascular disease.^[5]^

The rapid increase in the prevalence of obesity, and its high disease burden, strengthens the need to identify, implement, and evaluate evidence-based interventions that address this problem.^[6]^ The existing evidence does not support the use of low- or moderate-intensity counselling alone in the treatment of obesity.^[7]^ Whereas complex, multipronged interventions have resulted in clinically significant weight loss (over 5%) in overweight and obese adults.^[8]^ Towards that end, the US Preventive Services Task Force recommends these intensive interventions partially because more patient contact in the first year results in greater, more sustainable weight loss.^[9]^

### Lifestyle and obesity

1.2

A healthy lifestyle has been associated with a lower prevalence of obesity.^[10]^ The positive effects of regular physical activity on health and mortality are well established. Physical activity plays an important role in the prevention of various chronic diseases, such as cardiovascular disease, obesity, diabetes mellitus, osteoporosis, and colon cancer.^[11]^ However, in Europe, more than half of the adult population does not achieve the recommended levels of daily physical activity.^[12]^ Furthermore, sedentarism, defined as low levels of energy expenditure (≤1.5 MET basal metabolic rate), is related to multiple health problems: higher risk of diabetes, cardiovascular disease, cancer, and all causes of death.^[13]^ Generally, the most obesity-inducing lifestyle choice is unhealthy eating habits. Diet has been directly associated with the prevalence and development of obesity. In this regard, the Western diet, characterized by high energy density, high fat content, and low consumption of fiber, is associated with higher rates of obesity,^[14]^ including higher plasma glucose levels and an unfavorable lipid profile.^[15]^ On the other hand, the Mediterranean diet is correlated with lower rates of obesity in a population with high cardiovascular risk, which results in reduced insulin resistance and less inflammation.^[16]^

### Obesity and arterial aging

1.3

Obesity is associated with arterial health.^[17]^ In the EVIDENT study, sedentarism, low physical activity, and certain nutritional patterns were found to correlate with hemodynamic measures of arterial aging, such as the peripheral augmentation index (PAIx).^[18–20]^ There are numerous devices available for evaluating central hemodynamics,^[21]^ including a wrist-worn tonometry device developed by Microsoft Research^[22]^ that are both easy and convenient to use.

### Mobile interventions for improving lifestyle and weight loss

1.4

The use of smartphone applications applied to the field of medicine is in progressive increase.^[23]^ mHealth includes the use of mobile phones, patient monitoring devices, and other wireless systems that can be used in the prevention, diagnosis, and treatment of chronic diseases including but not limited to type 2 diabetes and hypertension^[24–26]^ in addition to promoting a healthy lifestyle.^[27]^ A recent meta-analysis showed that mobile technology tools can result in a mean reduction of 41 minutes per day of sitting time.^[28]^ The potential of these applications to change lifestyles in the population is very promising, but long-term studies are needed to evaluate their efficacy over time.^[29]^ A review of the topic quantified the effect of these interventions as a decrease of on average 1.44 kg in body weight and of 0.24 units on the BMI.^[30]^ These values are very similar to those shown in the review by Flores Mateo et al.^[31]^ Taken together, these results indicate that mobile interventions decrease adiposity (Evidence Class IA)^[29]^ with an efficacy dependent on and proportional to the frequency with which they are used.^[32]^

### Weight loss and quality of life

1.5

Interventions that aim to reduce obesity in adults through a combination of diet and physical exercise have achieved improvements in quality of life,^[33]^ with sustainable long-term effects (24 months). However, according to a recent meta-analysis, these improvements were achieved primarily on a physical level, not a mental one.^[34]^

In the previous study (EVIDENT 2), an improvement was obtained in terms of increased self-reported physical activity and an attributable effect in improving dietary habits in general population,^[35,36]^ using a smartphone application. In this study protocol we present the third phase of the EVIDENT study where the following developed version of the application will be used in a population of special vulnerability due to its increased cardiovascular risk, obese, or overweight people.

The objective of this research is to assess the impact of the EVIDENT 3 application on weight loss when combined with traditional primary care lifestyle modifications in overweight or obese subjects. Secondary outcomes include changes in physical activity, sedentarism, caloric intake, quality of life, arterial aging, and pro-inflammatory markers.

## Methods

2

### Design and setting

2.1

This is a randomized, multicentre clinical trial with 2 parallel groups. The study will be conducted in a primary care setting. The Research Unit group from La Alamedilla Health Center, Biomedical Research Institute of Salamanca (IBSAL), will coordinate the project on 5 sites from the Network for Preventive Activity and Health Promotion (REDIAPP) (Salamanca, Valladolid, Cuenca, Palma de Mallorca, and Zaragoza).

### Study population

2.2

All current patients of this 5 health centers will be eligible for this study. Once inclusion/exclusion criteria are met (detailed below), a healthcare professional will provide study subjects with oral and written information about the study. Informed consent will be obtained prior to any trial proceedings.

Inclusion criteria: subjects 20 to 65 years of age, BMI ≥27.5 and <40 kg/m^2^, classified based on sedentarism (<3 20 minutes sessions of vigorous intensity physical activity per week; ≥5 30 minutes sessions of moderate intensity physical activity [including walking] per week; or ≥5 sessions of any combination of moderate and vigorous intensity physical activity).^[37]^

Exclusion criteria: subjects with any of the following conditions will be excluded: musculoskeletal disease restricting walking; low-calorie diet prescribed and/or controlled by a healthcare professional or other weight loss program; use of other applications with the objective to lose weight; bariatric surgery in the past or planned in the next 12 months; treatment with any pharmaceutical, natural, or homeopathic formulation for weight loss; personal history of NYHA Grade II or higher heart failure^[38]^; type 2 diabetes; oncological disease actively being treated; terminal status; pregnancy; people living in the same household as another study participant; other causes at the investigator's discretion that prevent inclusion.

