#### Physical activity

2.6.2

Physical activity will be measured using both objective and subjective methods. Data from both self-reported and objective methods will be analyzed and published in study-derived manuscripts.

The primary means for quantifying physical activity objectively will be the number of steps/d measured by an Actigraph GT3X accelerometer (ActiGraph, Shalimar, FL), which has been previously validated.^[44]^ Output from the ActiGraph is in the form of activity “counts,” where 1 count is equivalent to 16 mg per second. Activity “counts” are recorded to the internal memory of accelerometers by converting acceleration units over a given period.^[45]^ The change in the quantity and intensity of the physical activity expressed in counts per minute, time dedicated to low, moderate, and high/very vigorous activity will be determined. All subjects included will wear the accelerometer on the right side of the waist, with an elastic band, for 7 consecutive days. Data will be recorded at 1-minute intervals. The intensity of the physical activity (low, moderate, or high) will be determined according to the cut-off points proposed by Freedson et al,^[46]^ sedentary activity (<100 counts/min), light (100–1952 counts/min), moderate (1952–5724 counts/min), vigorous (5724–9498 counts/min), and very vigorous (>9498 counts/min). The amount of physical exercise will be estimated in MET/h/wk, and active persons will be engaging in at least 30 minutes of moderate activity 5 days per week, or at least 20 minutes of vigorous activity 3 days per week, or who reach 450 MET/min/wk.^[47]^ Criteria for considering an accelerometer session to be valid include a minimum of 5 days, including at least 1 day of the weekend. Sequences of ≥10 consecutive zeros will indicate that the participant has not worn the device and will not be taken into account in the analysis.

The short version of the International Physical Activity Questionnaire (IPAQ)^[48]^ will be used to measure activity subjectively. The IPAQ is a self-reported questionnaire that evaluates sitting and active time in the last 7 days differentiating between walking, moderate-intensity, and vigorous-intensity activities, according to the energy expenditure estimated for each of them (3.3, 4.0, and 8.0 metabolic equivalents of task [MET], respectively). It allows the MET-min/wk to be calculated and subjects to be classified according to 3 activity levels (low, intermediate, and high).

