#### Standard counselling (CG and IG)

2.7.1

Both groups (control and intervention) will receive 5 minutes of counselling at the end of the baseline visit and prior to randomization. Advice on physical activity will be in compliance with the current international recommendations for the general population. The health benefits of physical activity and the recommendation to complete at least 30 minutes of moderate activity 5 days a week, or 20 minutes of vigorous activity 3 days a week, will be explained. Counselling on food will be in compliance with the plate method,^[59]^ in which a plate is divided into 4 parts: half the plate for salad or vegetables, one fourth for proteins (white meat preferred over red meat), and the final fourth for carbohydrates. In addition, a medium-sized piece of fruit and a skimmed dairy product should be consumed for dessert.

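### The sedentarism inclusion criterion contradicts itself and the protocol's own definition of an active person, so the rule on who is eligible is wrong as printed

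*Protocol article*

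**What the plan says.** Section 2.2 (Study population) lists three things under inclusion criteria: age, BMI and activity status. The activity part has three limbs:

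- Part A (vigorous sessions): "classified based on sedentarism (<3 20 minutes sessions of vigorous intensity physical activity per week"
- Parts B (moderate sessions) and C (both kinds together), printed one after the other: "≥5 30 minutes sessions of moderate intensity physical activity [including walking] per week; or ≥5 sessions of any combination"

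Section 2.6.2 (Physical activity) says that "active persons will be engaging in at least 30 minutes of moderate activity 5 days per week". It then adds two further routes to the same status: "or at least 20 minutes of vigorous activity 3 days per week, or who reach 450 MET/min/wk". Section 2.7.1 (Standard counselling) gives both groups "the recommendation to complete at least 30 minutes of moderate activity 5 days a week", with the vigorous threshold as the alternative. Section 1.2 describes sedentarism as low energy expenditure, at or below 1.5 MET.

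**The concern.** Part A sets an upper bound on activity, as a definition of sedentarism should. Parts B and C set lower bounds. Part B is the moderate-activity threshold by which section 2.6.2 calls a person active, and the goal towards which section 2.7.1 counsels everyone. Part C lies at a similar level. One label therefore covers people on opposite sides of the line it is meant to draw, and the limbs end in *or*, which does not say clearly how they combine.

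This is an eligibility rule for a trial at 5 sites (section 2.1). If screening follows the printed words, people already at the activity goal can enter. If screening staff guess at the intent, the enrolled population depends on the guess. What is at stake is the description of who was studied and, possibly, how far steps/d and sitting time, both named secondary outcomes in section 2.6, can still move.

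**Working it through.** **The plan's own figure.** The only design figure is the sample size in section 2.3: SD 12 kg, difference 3 kg, α 0.05 (taken as two-sided), power 80%, 15% loss. Per group, n = 2 × [12 × (1.960 + 0.842) / 3]² ≈ 251.2. Dividing by 0.85 gives 295.5, so 296 per group and 592 in total, as stated. The activity criterion does not enter this calculation.

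**Set-up for the criterion.** Let v be the weekly number of vigorous 20-minute sessions and m the number of moderate 30-minute sessions, each from 0 to 7. That gives 8 × 8 = 64 patterns. From section 2.2:

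- A: v < 3
- B: m ≥ 5
- C: v + m ≥ 5

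From section 2.6.2, a person is active by the session rules if m ≥ 5 or v ≥ 3, with one session counted as one day. Each reading was run over all 64 patterns; (v, m) denotes a pattern.

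| Reading | Eligible | Of these, active by session rules | (0,0) | (0,5) |
|---|---|---|---|---|
| Printed: A or B or C | 61 | 46 | in | in |
| Printed: A and B and C | 9 | 9 | out | in |
| Printed: A and (B or C) | 12 | 9 | out | in |
| Signs of B and C changed to <5, *or* kept | 49 | 34 | in | in |
| Signs changed, all three required | 12 | 0 | in | out |

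These are counts of patterns, not shares of any population.

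**What the table shows.**

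1. Read with *or*, the excluded patterns are those with v ≥ 3, m < 5 and v + m < 5, which are only (3,0), (3,1) and (4,0). Adding activity can turn exclusion into eligibility: (3,0) is out, while (3,2) and (7,7) are in.
2. Under both *and* readings, the person with no activity at all is out.
3. Under all three readings of the printed text, (0,5) is in, although section 2.6.2 calls that person active.
4. Changing the signs alone is not enough. With *or* kept, 34 of the 49 eligible patterns are still active.

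**The MET route.** Section 2.6.2 gives weights for walking, moderate and vigorous activity of "3.3, 4.0, and 8.0 metabolic equivalents of task [MET], respectively". They are stated for the questionnaire; using them against the 450 threshold (read as MET-min/wk) is an assumption made here. One moderate session is 30 × 4.0 = 120 and one vigorous session is 20 × 8.0 = 160, so weekly MET-min = 160v + 120m.

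- Part B at its minimum: 5 × 120 = 600. If the sessions are walking, 5 × 30 × 3.3 = 495. Both exceed 450.
- The three patterns admitted by A and (B or C) that are not active by the session rules are (1,4) = 640, (2,3) = 680 and (2,4) = 800. All exceed 450.
- Of the 12 patterns under the corrected rule, three still reach 450: (0,4) = 480, (1,3) = 160 + 360 = 520 and (2,2) = 320 + 240 = 560. The next highest, (2,1), is 440.

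**The case against.** The strongest reply is that this is a slip in a journal article that condenses a fuller protocol. Part A carries the expected sign, the criterion cites a published definition, and nothing shows that the sites screened from this wording or differed from one another. That stands as far as consequences go: what happened at the sites is unknown. It does not rescue the text, because the rule is stated, stated wrongly, and corrected nowhere in the document.

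A second reply is that the objective in section 1.5 names overweight or obese subjects with no sedentary restriction, that the primary outcome is weight, and that the two arms are randomised within whatever population is enrolled. This also stands. A reader might infer that the primary comparison is compromised, or that the trial forfeits a claim about sedentary adults. The documents support neither: sedentarism restricts the population only in section 2.2, and the 592 does not depend on it.

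A reader might also infer that the steps/d effect shrinks in proportion to the share of participants already active. That needs a figure for the share and an assumption that such people gain nothing; the documents give neither. Nor can one say that the rule screens out almost nobody, since no distribution of activity in the population is given.

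**Conclusion.** The criterion is wrong as printed. It contradicts itself (part A against parts B and C) and contradicts sections 2.6.2 and 2.7.1, and no way of joining the limbs removes the fault. The finding is one of logic. It rests on reading combined sessions as v + m and on matching sessions per week to days per week. Its reach is eligibility, to whom the results apply, and possibly the room for change in steps/d and sitting time; the size of that last effect cannot be derived from the documents. The sample size for weight is unaffected.

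One might assume that the corrected rule is the exact complement of the active definition in section 2.6.2. It is not: that definition has a 450 MET-min/wk route and no combined-session rule, and with the weights used above 3 of the 12 patterns admitted by the corrected rule still count as active.

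**What to change.** 1. Correct both the signs and the connective in section 2.2, so that a person counts as sedentary only if all three hold per week: fewer than 3 vigorous 20-minute sessions, fewer than 5 moderate 30-minute sessions, and fewer than 5 sessions combined. Check the wording against the definition that the section cites, which is not available here.
2. Reconcile this with the 450 MET-min/wk route in section 2.6.2, for example by stating whether that route applies at screening or only to classifying measured activity.
3. Confirm that the screening form at all 5 sites carries the corrected text.
4. If the operative protocol has the printed wording, amend it and flag participants who entered through part B or C without meeting the corrected rule.

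Cost: an erratum if only the article is wrong. If the operative protocol is wrong, a short amendment put to the Salamanca committee and those of the 4 collaborating centres (section 2.13), plus the work of flagging. No new measurement is needed.

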### Sample size

2.3

The sample size calculation was performed for the primary study endpoint of weight loss. Accepting an α risk of 0.05 and a β risk of 0.20, with an standard deviation (SD) of 12 kg, estimated in subjects from EVIDENT 2 study,^[35]^ 592 subjects would be needed (296 per group) to detect a decrease in weight of ≥3 kg^[39]^ in the intervention group (IG) versus the control group (CG), taking into consideration a 15% loss to follow-up. This effect size represents a 3% to 5% difference between groups, which should produce clinically relevant health benefits.^[40]^ To minimize dropouts, a reminder of the next visit will be provided at the end of each visit, as well as 2 phone calls 15 and 5 days prior.

### Randomization

2.4

Participants will be randomly assigned to either the IG or the CG. Randomization will be performed after informed consent is obtained. The allocation sequence will be generated through a standardized computer programme (Epidat 4.2)^[41]^ by an independent researcher and concealed until the trial arms are assigned.

### Procedures

2.5

Each participant will complete an initial visit and 2 follow-up visits at 3 and 12 months after study initiation (Fig. 1). Baseline data will be collected by a research nurse. The IG will complete 2 additional appointments with a different nurse performing the measurements. The first one will occur 7 days from the baseline in which the application will be explained and the second one will be during a phone call 15 days from the baseline visit to answer any questions on how to use the application.

**Figure 1 F1:**
[figure not shown]
Study flowchart.

### Primary and secondary outcomes

2.6

The primary outcome will be weight loss (kg). Secondary outcomes will include change in the physical activity (steps/d) measured by accelerometer, sitting time (min/wk), caloric intake (kcal/d), quality of life, arterial aging, and pro-inflammatory markers. All outcomes will be measured at baseline, 3, and 12 months after randomization.

#### Weight loss

2.6.1

Body weight will be measured twice, with the subject barefoot and wearing light clothing, using a homologated electronic balance (Scale 7830; Soehnle Professional GmbH & Co, Backnang, Germany) after proper calibration (precision ± 0.1 kg). Height will be measured with the subject barefoot in the standing position to record the average of 2 readings rounded to the nearest centimeter, using a portable system (Seca 222; Medical scale and measurement system, Birmingham, UK). BMI will be calculated by weight (kg) divided by height squared (m^2^). Following the recommendations of the Spanish Society for the Study of Obesity (SEEDO),^[42]^ waist circumference will be measured in duplicate, using a flexible tape parallel to the floor, at the level of the midpoint between the last rib and the iliac crest, with the subject standing without clothing, after inspiration. Hip circumference will be similarly measured at the level of the trochanters. Body composition will be determined using an Inbody 230 analyzer^[43]^ that estimates total body water, dry lean mass, body fat mass, skeletal muscle mass, body fat percentage, distribution of lean body mass, ratio of segmental lean mass, and impedance of each body segment.

#### Physical activity

2.6.2

Physical activity will be measured using both objective and subjective methods. Data from both self-reported and objective methods will be analyzed and published in study-derived manuscripts.

The primary means for quantifying physical activity objectively will be the number of steps/d measured by an Actigraph GT3X accelerometer (ActiGraph, Shalimar, FL), which has been previously validated.^[44]^ Output from the ActiGraph is in the form of activity “counts,” where 1 count is equivalent to 16 mg per second. Activity “counts” are recorded to the internal memory of accelerometers by converting acceleration units over a given period.^[45]^ The change in the quantity and intensity of the physical activity expressed in counts per minute, time dedicated to low, moderate, and high/very vigorous activity will be determined. All subjects included will wear the accelerometer on the right side of the waist, with an elastic band, for 7 consecutive days. Data will be recorded at 1-minute intervals. The intensity of the physical activity (low, moderate, or high) will be determined according to the cut-off points proposed by Freedson et al,^[46]^ sedentary activity (<100 counts/min), light (100–1952 counts/min), moderate (1952–5724 counts/min), vigorous (5724–9498 counts/min), and very vigorous (>9498 counts/min). The amount of physical exercise will be estimated in MET/h/wk, and active persons will be engaging in at least 30 minutes of moderate activity 5 days per week, or at least 20 minutes of vigorous activity 3 days per week, or who reach 450 MET/min/wk.^[47]^ Criteria for considering an accelerometer session to be valid include a minimum of 5 days, including at least 1 day of the weekend. Sequences of ≥10 consecutive zeros will indicate that the participant has not worn the device and will not be taken into account in the analysis.

The short version of the International Physical Activity Questionnaire (IPAQ)^[48]^ will be used to measure activity subjectively. The IPAQ is a self-reported questionnaire that evaluates sitting and active time in the last 7 days differentiating between walking, moderate-intensity, and vigorous-intensity activities, according to the energy expenditure estimated for each of them (3.3, 4.0, and 8.0 metabolic equivalents of task [MET], respectively). It allows the MET-min/wk to be calculated and subjects to be classified according to 3 activity levels (low, intermediate, and high).

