#### Sedentary lifestyle

2.6.3

The sitting time (min/wk) will be assessed using the ActivPal device. ActivPAL has been proven to be a practical, reliable, and valid instrument for objectively recording sedentary activity.^[49]^ This device will be adhered to the front of the thigh of each participant, between the knee and the trunk, using an adhesive strip. Participants will use the devices for 7 days at each follow-up visit (baseline, 3, and 12 months). This device is used to estimate the average minutes of activity per day, average minutes spent sitting per day, and average number of steps per day. We will use cut-off points for the categorization of the sedentary behavior (0–5 counts/15 s) collected through the ActivPal devices, as proposed by Atkin et al.^[50]^

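### The 10-minute zero-count non-wear rule cannot tell device removal from still sitting, so it inflates accelerometer counts/min and can bias the change in that supporting measure in either direction

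*Protocol article*

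**What the plan says.** All the relevant statements on the accelerometer stand in section 2.6.2 (Physical activity) of the protocol article.

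- Epoch: "Data will be recorded at 1-minute intervals".
- Non-wear: "Sequences of ≥10 consecutive zeros will indicate that the participant has not worn the device", and such runs are left out of the analysis.
- Lowest intensity band: "sedentary activity (<100 counts/min", which has no lower limit and so includes zero.
- Main objective measure: "The primary means for quantifying physical activity objectively will be the number of steps/d measured by an Actigraph GT3X accelerometer".
- Further measure: "The change in the quantity and intensity of the physical activity expressed in counts per minute", together with time in low, moderate and high or very vigorous activity.
- Valid session: "a minimum of 5 days, including at least 1 day of the weekend".

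Sitting time is a separate outcome from a separate thigh-worn device (section 2.6.3, ActivPal): "Participants will use the devices for 7 days at each follow-up visit (baseline, 3, and 12 months". The zero-run rule is stated for the accelerometer, not for that device. Section 2.9 compares changes from baseline between arms by ANCOVA at 3 and 12 months, adjusted for the baseline value.

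**The concern.** With 1-minute epochs, ten consecutive zeros are ten minutes. A person who sits still for that long with the device on gives the same record as a person who has taken it off. The section treats a single zero-count minute as sedentary behaviour but a run of ten as no data.

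Removing worn minutes that carry no counts leaves the total count unchanged and shortens the time it is divided by. The level of counts/min therefore rises, and it rises more for people who sit still for longer. If the app changes how long people sit, the amount removed differs between visits and between arms. The error then enters the treatment comparison for counts/min instead of cancelling.

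**Working it through.** The article gives no wear time, counts/min or sitting-bout data, so there is no stated figure to reproduce. The rule, the epoch and the bands come from section 2.6.2. Everything marked as assumed is mine.

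**1. Level.** Let C be total counts per day, W worn minutes and Z worn sitting minutes deleted by the rule. I take counts/min as the mean over retained minutes, since deleted runs are left out of the analysis. The true mean is C/W and the mean under the rule is C/(W−Z). The relative inflation is Z/(W−Z), whatever C is. With W = 840 (assumed):

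- Z = 60: 60/780 = 7.7%
- Z = 120: 120/720 = 16.7%
- Z = 180: 180/660 = 27.3%
- Z = 240: 240/600 = 40.0%

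Accelerometer sedentary minutes fall by Z.

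**2. How readily sitting is deleted.** A simulated 60-minute sitting bout, with each minute independently zero with assumed probability p, loses this share to each run limit:

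| p | 10 min | 20 min | 60 min |
|---|---|---|---|
| 0.80 | 27% | 4% | 0% |
| 0.90 | 61% | 27% | 0.1% |
| 0.95 | 82% | 59% | 5% |

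**3. Change when deleted sitting becomes activity.** If d deleted minutes turn into activity at r counts/min, the true change is d·r/W. The change under the rule is (C + d·r)/(W−Z+d) − C/(W−Z) = d(r − m′)/(W−Z+d), where m′ = C/(W−Z). It is negative whenever r < m′. With C = 252,000 (true mean 300), Z = 180 and d = 30 (all assumed), m′ = 381.8:

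- r = 200: true +7.1, rule −7.9 (sign reversed)
- r = 500: true +17.9, rule +5.1 (shrunk)
- r = 1000: true +35.7, rule +26.9 (shrunk)
- r = 2500: true +89.3, rule +92.1 (slightly enlarged)

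**4. Change within retained minutes.** With the same C and Z, suppose 30 retained minutes rise from 300 to 2500 counts/min and Z does not move. The true change is 66,000/840 = +78.6, and the rule gives 66,000/660 = +100.0, which is 27% too large.

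**5. Mixed case.** Take C = 250,000 (assumed) and let 41 min/day of sitting, the reduction cited in section 1.4, become activity at 500 counts/min (assumed). Let f be the share of those minutes that lay in deleted runs. The true change is 20,500/840 = +24.4. Under the rule it is 270,500/(840−Z+41f) − 250,000/(840−Z):

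| f | Z = 120 | Z = 180 | Z = 240 |
|---|---|---|---|
| 0 | +28.5 (17% too large) | +31.1 (27% too large) | +34.2 (40% too large) |
| 0.25 | +23.2 (5% too small) | +24.8 (2% too large) | +26.6 (9% too large) |
| 0.5 | +18.1 (26% too small) | +18.7 (23% too small) | +19.3 (21% too small) |
| 1 | +8.2 (66% too small) | +7.1 (71% too small) | +5.3 (78% too small) |

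**6. Measures that do not move.** A deleted minute has zero counts, so it never belonged to the light, moderate, vigorous or very vigorous band, and those minutes are unchanged. It carries essentially no steps, so the daily step total stands unless it is scaled to wear time or days are dropped for short wear. The article states neither.

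**The case against.** The strongest reply is that the trial's named outcomes are shielded. The primary outcome is weight, the accelerometer outcome in section 2.6 is steps/d, and sitting time comes from the ActivPal. That stands, and it limits the point to counts/min and accelerometer sedentary time. For the latter, section 2.6.2 gives a cut-off but does not list the time itself among the quantities to be determined.

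A reader might infer that the rule necessarily shrinks the intervention effect. The working does not support this: the direction depends on which minutes change and to what intensity. The counselling given to both arms (section 2.7.1) recommends moderate or vigorous activity, so light activity replacing sitting is only one possible pathway. Expressing each change as a percentage of its own baseline would also overstate the shrinkage, because the baseline under the rule is already inflated. Section 2.9 compares absolute changes.

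A reader might also infer that this sample must be rich in 10-minute zero runs because it was selected as sedentary. Section 2.2 defines sedentarism by weekly exercise sessions, not by sitting bouts, so the size of Z cannot be drawn from the article.

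Finally, nothing in the article favours 60 minutes over another limit, and a longer limit has its own error. That is fair. It is why a second limit should be reported, but it does not rescue a limit that conflicts with the section's own sedentary band.

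**Conclusion.** The point holds for counts/min and accelerometer sedentary time. As written, the rule deletes genuine still sitting, and the upward bias in the level of counts/min follows by algebra for any Z above zero. Its size, about 8% to 40% for Z from 60 to 240, rests on the assumed 840 worn minutes.

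The bias in the between-arm change has no fixed sign. In the mixed case it runs from 78% too small to 40% too large, and the sign can reverse when deleted sitting becomes light activity below the inflated mean. ANCOVA on the baseline value does not correct this, because the distortion depends on sitting at 3 and 12 months. The documents do not show that the bias will be large in this trial or that it will run against the intervention. This is a minor-to-moderate flaw in a supporting measure, with no bearing on the primary outcome.

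**What to change.** In section 2.6.2, replace the limit of ten zero minutes with a longer run, for example 60 or more consecutive zero-count minutes. Apply it identically at baseline, 3 and 12 months and in both arms. Report counts/min under a second limit, for example 90 minutes, as a sensitivity analysis. Where the ActivPal was worn in the same week, use its record to check whether a long zero run was removal or sitting.

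The cost is a changed processing parameter and a second run on stored data, with no new visits or measurements. The downside is that removals shorter than the limit are kept as sedentary wear. Keeping U unworn minutes lowers counts/min by U/(W+U): with W = 840, 30/870 = 3.4% for 30 minutes a day and 60/900 = 6.7% for 60. The two limits reported side by side show how far the result depends on the choice.
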